# CELEB trial: Comparative Effectiveness of Lung volume reduction surgery for Emphysema and Bronchoscopic lung volume reduction with valve placement: a protocol for a randomised controlled trial

**DOI:** 10.1136/bmjopen-2017-021368

**Published:** 2018-10-17

**Keywords:** COPD, lung volume reduction, thoracic surgery, emphysema

## Abstract

**Introduction:**

Although lung volume reduction surgery and bronchoscopic lung volume reduction with endobronchial valves have both been shown to improve lung function, exercise capacity and quality of life in appropriately selected patients with emphysema, there are no direct comparison data between the two procedures to inform clinical decision-making.

**Methods and analysis:**

We describe the protocol of the CELEB study, a randomised controlled trial which will compare outcomes at 1 year between the two procedures, using a composite disease severity measure, the iBODE score, which includes body mass index, airflow obstruction, dyspnoeaand exercise capacity (incremental shuttle walk test).

**Ethics and dissemination:**

Ethical approval to conduct the study has been obtained from the Fulham Research Ethics Committee, London (16/LO/0286). The outcome of this trial will provide information to guide treatment choices in this population and will be presented at national and international meetings and published in peer-reviewed journals. We will also disseminate the main results to all participants in a letter.

**Trial registration number:**

ISRCTN19684749; Pre-results.

Strengths and limitations of this studyThis is a randomised controlled trial.There is a strict patient selection criterion for this trial based on previous research.Currently there is equipoise between the two interventions being compared.Due to the nature of the interventions it is not possible to double-blind the trial.It may be difficult to obtain longer term outcomes as patients may cross over after the 12-month period of the trial.

## Introduction

Chronic obstructive pulmonary disease (COPD) is a common and disabling condition which is now the third largest cause of death worldwide.^1^ Breathlessness, exercise limitation and mortality in COPD are all associated with increased lung volumes occurring due to airflow obstruction and increased lung complicance.^2^ The condition is progressive and despite optimum care including smoking cessation, pharmacotherapy and pulmonary rehabilitation, many patients remain breathless and limited in everyday activities.^3 4^ Surgical and bronchoscopic approaches to lung volume reduction are available which can bring substantial benefits in appropriately selected individuals, though both are also associated with some risk.

Lung volume reduction surgery (LVRS) involves removing the worst affected area of emphysematous lung, which means that the remaining healthier and less compliant lung can function more effectively, with the respiratory muscles working at less of a mechanical disadvantage.^5^ LVRS has been shown to improve survival, exercise capacity and quality of life in appropriately selected patients with heterogeneous emphysema and poor exercise capacity,^5–9^ and is therefore recommended in national and international guidelines for the management of COPD.^1 10 11^ However, uptake has been limited, due in part to exaggerated concerns about surgical morbidity and mortality.^12^ In modern clinical practice, morbidity and mortality from the procedure are substantially lower^9 13^ than was the case in trials conducted around the turn of the century.^5 6^

An alternative approach to resecting the target area of lung is to place endobronchial valves occluding the airways supplying a particular lobe. This form of bronchoscopic lung volume reduction (BLVR) can produce lobar atelectasis, and is intended to achieve similar benefits to LVRS but with less morbidity.^14–24^ The approach is only effective in the absence of interlobar collateral ventilation (CV).^23 25^ If this is present, air can enter the target lobe from an adjacent lobe and atelectasis does not occur. In patients with a heterogeneous pattern of emphysema and intact interlobar fissures, valve placement can produce significant improvements in lung function, exercise capacity and health status.^23 26–28^ Yet complications do occur, in particular pneumothorax which occurs in up to 30% of cases^28^ and can on occasion be fatal, as well as exacerbation-like events. Valve expectoration or misplacement can necessitate additional procedures.

Patients with heterogeneous emphysema and intact interlobar fissures may benefit from either BLVR or LVRS, but there are no direct comparison data on the relative value of the two procedures to guide clinical decision-making.

The CELEB study is a multicentre, randomised controlled parallel group trial that opened for recruitment in October 2016. Patients who are considered to be suitable candidates for both forms of targeted lung reduction therapy will be randomised to either BLVR or LVRS. The primary aim of the CELEB study is to determine whether LVRS procedures can achieve a greater health benefit at 1 year than BLVR. This will be determined using change in the iBODE index, a composite measure of COPD severity (made up of body mass index (BMI), airflow obstruction, dyspnoeaand exercise capacity (the incremental shuttle walk test)).^29^ Change in BODE score has been found to be a good predictor of survival in LVRS patients.^30^ Health resource utilisation will also be compared between treatment arms. Clinical efficacy will be assessed over a 12-month period. The study is set up as a superiority trial and will be conducted, analysed and reported according to the Consolidated Standards of Reporting Trials statement for randomised controlled trials. This paper will outline the protocol for the CELEB study (version 2.0, 19 February 2016).

## Methods and analysis

### Participants

Patients will be recruited from outpatient clinics at UK hospital sites which have an established multidisciplinary team (MDT) meeting dedicated to identifying suitable candidates for LVR.^31^ Patients will be eligible for the study if they fit the following criteria: significant airflow obstruction (forced expiratory volume in 1 s (FEV_1_) <60% predicted), limiting breathlessness (Medical Research Council (MRC) dyspnoea score >3), significant hyperinflation (total lung capacity >100% predicted, residual volume (RV) >170% predicted) and are considered, using CT and perfusion scan, to have a heterogeneous emphysema pattern with intact interlobar fissures (>90%). They must also not have smoked for at least 3 months. Patients fitting these criteria will be identified from outpatient clinics and put forward for discussion at the MDT meeting. Patients will be excluded if they have pulmonary fibrosis or any other major comorbidity that could affect survival or mean that LVR procedures are unlikely to be effective. Patients with PaO_2_ <7.0 kPa and/or PaCO_2_ >7.0 kPa will also be excluded. The MDT will make a decision on whether a patient is suitable for both interventions and if so, that there is equipoise between the treatment options. It is only after this is agreed that the screening visit will be arranged and consent taken.

### Interventions

LVRS will be carried out by a thoracic surgeon under general anaesthetic using a unilateral video assisted thoracoscopic surgery (VATS) approach. The precise operation will be at the discretion of the surgeon, intended to remove the most emphysematous area of lung, leaving the best quality lung behind and minimising air leaks and other complications. The patients will initially go to the high dependency unit postoperatively, and postoperative management will include attention to wound discomfort, management of chest drains and prompt mobilisation. Patient management, discharge and initial follow-up will be determined by their clinical team.

BLVR will be performed via bronchoscopy by an operator experienced in placing endobronchial valves. The procedure will be performed under conscious sedation or general anaesthetic if necessary, with endobronchial valves placed to occlude the target lobe. A chest X-ray will be performed 1 hour after procedure and participants will spend three nights after procedure as an inpatient routinely in case a pneumothorax occurs. They will be discharged with written advice about the signs of pneumothorax and what to do if these occur. Procedures including valve adjustment and replacement will be permitted to ensure treatment is optimised.

Participants will be followed up in clinic routinely about 3 months after discharge. Other clinic attendances will depend on clinical need with further investigations and procedures determined by their responsible clinician. Patients will receive a phone call from the study team at 1 month and at 6 and 9 months. There will be a final clinic visit at 12 months. A summary of the trial assessment is shown in table 1.

**Table 1 T1:** Summary of trial assessments

	Visit 1 Baseline	Visit 2 Chartis measurement	Visit 3 Admission for procedure	Visit 4 1 month safety phone call	Visit 5 3 months’ follow-up	6 months	9 months	Visit 6 1 year follow-up
History, physical exam	x				x			
Informed consent	x							
FFM	x							x
MRC score	x				x			x
CAT score	x				x			x
Full pulmonary function*	x				x			x
CT thorax	x				x			
iSWT	x				x			x
Activity monitor given for 7 days	x							x (7 days prior to visit)
Activity monitor collected		x						x
c-PPAC score		x						x
Bronchoscopy with Chartis measurement of collateral ventilation		x						
Randomisation		x						
Treatment intervention: LVRS or BLVR			x					
Health resource utilisation (CSRI questionnaire)					x	x	x	x

*Spirometry, gas transfer, plethysmographic lung volumes, capillary blood gases.

BLVR, bronchoscopic lung volume reduction; CAT, COPD Assessment Test; c-PPAC, clinical visit version of the PROactive Physical Activty for COPD instrument; CSRI, Client Sociodemographic and Service Receipt Inventory; FFM, fat-free mass; iSWT, incremental shuttle walk test; LVRS, lung volume reduction surgery; MRC, Medical Research Council.

### Outcomes

The primary outcome will be the change in iBODE score^32^ at 12 months from baseline. The iBODE incorporates the incremental shuttle walk test (iSWT), BMI, FEV_1_ and the MRC dyspnoea score. Possible scores range from 0 to 10, with 10 with increasing scores associated with worsening mortality. The primary endpoint measures will be performed by staff blinded to treatment allocation and patients will be asked not to reveal this in order to reduce bias.

Secondary outcomes will be assessed at baseline, 3 months and 12 months. Changes in respiratory-related health status (COPD Assessment Test, CAT), health-related quality of life (HRQOL) using the EQ-5D-5L, RV and fat-free mass (FFM) will be evaluated. Physical activity will be measured using the clinical visit version of the PROactive Physcal Activity in COPD instrument.

The basis for the sample size calculation is the paper by Imfeld *et al* which addressed the response to LVRS.^30^ This compared the improvement in BODE score at 3 months after LVRS between survivors and non-survivors at 5 years. Long-term survivors had an improvement of 3.9 points at 3 months, the non-survivors had an improvement of 2.4 points (ie, a difference of 1.5 points). This difference is likely therefore to represent a clinically important difference between outcomes in the two LVR arms, being of sufficient magnitude to influence treatment decisions and is therefore a meaningful basis on which to power the study.

The study is powered on the basis of an average response to LVRS that will be the same as in the paper of Imfeld *et al* (ie, a fall of 3.1) and for BLVR that the improvement will be 1.6 (1.5 points less benefit). For practical purposes we have taken the BODE and the iBODE to be equivalent^29^ and so, assuming an SD of 1.8 for the change in BODE score and taking a 5% significance level and 90% statistical power, 34 patients would be required in each treatment arm. Allowing for 10% dropouts we will enrol 76 individuals.

### Assignment of interventions

All participants will undergo a fibre optic bronchoscopy to allow for assessment of the presence of CV using the Chartis system.^25^ This uses a balloon catheter, inflated in the target airway, with a flow sensor and a distal pressure metre. Pressure swings should continue with inspiration and expiration, but flow will diminish and then cease as the target lobe empties if there is no CV (CV −ve). If CV is present, the flow will continue (CV +ve). Subsequent participation in the trial depends on this. As the absence of CV in the target lobe is inclusion criterion, patients with CV are deemed to be screen failures and cannot proceed to randomisation (as they would not benefit from valve placement so there is no longer equipoise). However, they will still be suitable for a surgical approach and may go on to ‘open label’ LVRS. We will endeavour to follow these patients up at 12 months and their iBODE score will be evaluated. In some cases, CV cannot be assessed either because there is continuing low flow or an abrupt cessation in the flow trace suggesting obstruction. It may be possible to work round this by measuring the presence or absence of CV in the adjacent lobe (ie, the reciprocal position). Where CV is truly indeterminate, patients will be withdrawn from the study (ie, treated as CV positive).

If the person has a CV negative lobar target for treatment they will be immediately allocated randomly to one of the treatment arms, using an online system. Randomisation will be on a 1:1 basis based on a computer-generated random sequence with random block sizes generated by Sealed Envelope (London, UK). This will include stratification by site and by iBODE score to ensure matched numbers in both arms with an iBODE score of >7.

Patients, the study coordinator and those providing clinical care will not be blinded to treatment allocation. The assessors recording the components of the iBODE score will be blinded to reduce the potential for bias. Therefore, no unblinding process will be necessary.

### Data collection, management and analysis

At baseline a full medical history including exacerbations, hospital admissions and drug history will be taken. Pulmonary function tests (spirometry, plethysmography and gas transfer measurements) will be carried out according to the American Thoracic Society/European Respiratory Society recommendations, together with arterial blood gas analysis. Additional measures will include MRC dyspnoea score, health status (CAT), HRQOL (EQ-5D-5L) and FFM using bioimpedance. Two iSWTs will be carried out due to the learning effect seen following a test walk.^32^ Figure 1 provides a summary of the trial design.

**Figure 1 F1:**
[figure not shown]
Schematic outline of the trial design. BLVR, bronchoscopic lung volume reduction; BMI, body mass index; CAT, COPD Assessment Test; CV, collateral ventilation; CXR, chest X-ray; FFM, fat-free mass; iBODE, a composite score including BMI, airflow obstruction, dyspnoea and exercise capacity (incremental shuttle walk test); LVRS, lung volume reduction surgery; MDT, multidisciplinary team; MRC, Medical Research Council; PFT, pulmonary function tests, RV, residual volume; SWT, shuttle walk test; TLC, total lung capacity; VQ lung ventilation/perfusion scan.

Physical activity will be assessed using the PROactive Consortium patient-reported outcome tool for physical activity in COPD.^33–35^ Participants wear a DynaPort MoveMonitor accelerometer for 1 week as a measure of physical activity. At the end of this they complete the c-PPAC physical activity questionnaire which asks about the amount and difficulty of physical activity during the period covered by the monitor.

A cost-utility analysis will be carried out from a National Health Service (NHS) perspective using data from the trial. The relative value of the two approaches will be based on procedural cost, length of stay, days in hospital subsequently expressed as a cost per quality-adjusted life-year (QALY) together with data gathered using the Client Sociodemographic and Service Receipt Inventory which asks participants about their use of health and social services over the last 3 months. This will be completed at 3, 6, 9 and 12 months. They will be asked to report the frequency and intensity of their service use. Cost incurred in both arms may include: (1) medical and surgical services received as an inpatient; (2) healthcare visits in relation to COPD; and (3) COPD-related medication use. The total cost of individuals will be estimated by multiplying the resource use with national tariff used in the NHS. QALY will be estimated using EQ-5D-5L questionnaire. The five attributes of this questionnaire (mobility, self-care, usual activities, pain/discomfort/anxiety/depression) will be summarised into a single UK-derived preference-based utility score.

Outcome data analysis will be by intention to treat. Patients with missing data will be assumed to have had zero change from baseline. Unpaired t-tests will be used to compare mean response across the two groups: control and intervention. Mixed linear model procedure will be used to evaluate the effects of predefined covariables on dependent outcome variables.

Total costs will be calculated as the sum-product of resource use and unit cost for each patient. Incremental cost-effectiveness ratios (ICER) will be obtained by calculating the incremental costs divided by the incremental effects for the LVRS versus the BLVR group. Multivariate regression analysis will be used to adjust for baseline differences in health status between the trial groups. Uncertainty in the ICER will be addressed using bootstrapping and the estimation of cost-effectiveness acceptability curves. Estimates of ICERs will be compared with the £20 000–£30 000 per QALY threshold of cost-effectiveness recommended by the National Institute for Health and Care Excellence. No interim analyses are planned and the trial has no formal stopping guidelines.

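### The zero-change rule for missing data makes no exception for death, so a patient who dies scores better on iBODE than a survivor who worsens

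*Protocol article*

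**What the plan says.** All references are to the protocol article.

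- **Missing data** (Data collection, management and analysis): "Outcome data analysis will be by intention to treat. Patients with missing data will be assumed to have had zero change from baseline". The same paragraph names unpaired t-tests for the comparison of mean response. No section gives death a worst score, a rank, a place in a composite or any other separate treatment.
- **Primary outcome** (Outcomes): "The primary outcome will be the change in iBODE score^32^ at 12 months from baseline". On the scale: "Possible scores range from 0 to 10, with 10 with increasing scores associated with worsening mortality".
- **EQ-5D-5L** appears twice. Among the secondary change scores, Outcomes lists "health-related quality of life (HRQOL) using the EQ-5D-5L, RV and fat-free mass (FFM) will be evaluated". In the cost-utility text, "QALY will be estimated using EQ-5D-5L questionnaire".
- **Deaths are foreseen.** The Introduction says that both procedures carry some risk, discusses surgical mortality, and says of pneumothorax after valve placement that it "can on occasion be fatal, as well as exacerbation-like events".

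**The concern.** A patient who dies before 12 months has no 12-month iBODE. Intention to treat keeps that patient in the analysis, and the only printed rule for an absent value gives zero change. A survivor whose score rises by one point is then a worse result than a death.

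This conflicts with the reasons given for the endpoint. The Introduction supports it because change in BODE predicts survival after LVRS. Outcomes takes the 1.5-point target from the gap in BODE improvement between 5-year survivors and non-survivors in a surgical cohort. An endpoint valued for tracking mortality should not place an actual death above survival with deterioration.

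At stake is the primary comparison in a trial meant to inform the choice between surgery and valves. If one arm has more deaths, the rule makes that arm look better than a scoring that puts death at the bottom.

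**Working it through.** **Inputs from Outcomes:** mean change −3.1 (LVRS) and −1.6 (BLVR), SD 1.8, 5% significance, 90% power, 34 per arm, 10% dropout, 76 in total. **Assumed, because the document does not give them:** two-sided testing, baseline iBODE and numbers of deaths.

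**1. The plan's sample size.** The normal formula gives 2 × (1.960 + 1.282)² × 1.8² / 1.5² = 30.3, so 31 per arm. The exact t-test calculation gives 31.25, so 32. The stated 34 is within two patients of this, with t-test power of 92.3%. Then 34 / 0.9 = 37.8, so 38 per arm and 76 in total, as stated. The sample size is not in dispute.

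**2. Survivors who would score worse than a death.** With normal changes, the share above zero is 1 − Φ((0 − mean)/SD).
- LVRS: 1 − Φ(3.1/1.8) = 1 − Φ(1.72) = 4.3%.
- BLVR: 1 − Φ(1.6/1.8) = 1 − Φ(0.89) = 18.7%.

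Counting only whole-point worsening (cut at +0.5), the shares are 2.3% and 12.2%.

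**3. Cost of one death to its arm's mean, 38 per arm.** At assumed baseline 7, the worst score of 10 is a change of +3.

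| | Death at zero change | Death at score 10 |
|---|---|---|
| LVRS | 3.1/38 = 0.08 | 6.1/38 = 0.16 |
| BLVR | 1.6/38 = 0.04 | 4.6/38 = 0.12 |

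Zero change therefore charges about half (3.1/6.1) or a third (1.6/4.6) of the cost at the worst score.

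**4. Effect on the comparison.** With a fraction d of an arm dead and scored v, and survivors distributed N(m, 1.8²):
- arm mean = (1 − d)m + dv
- arm variance = (1 − d) × 1.8² + d(1 − d)(m − v)²
- SE = √((variance LVRS + variance BLVR)/38)
- power ≈ Φ(difference/SE − 1.96)

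With two LVRS deaths and no BLVR deaths (d = 2/38):
- v = 0: LVRS mean −2.94, difference 1.34, SE 0.423, power 88%.
- v = +3: LVRS mean −2.78, difference 1.18, SE 0.464, power 72%.

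| LVRS / BLVR deaths | Deaths at zero: difference (power) | Deaths at +3: difference (power) |
|---|---|---|
| 0 / 0 | 1.50 (95%) | 1.50 (95%) |
| 2 / 0 | 1.34 (88%) | 1.18 (72%) |
| 4 / 0 | 1.17 (78%) | 0.86 (40%) |
| 2 / 2 | 1.42 (92%) | 1.42 (83%) |

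With equal deaths the expected difference is the same under both scorings. With two BLVR deaths and none after LVRS the bias reverses: the difference is 3.1 − 1.6 × 36/38 = 1.58 at zero and 1.58 + 2 × 3/38 = 1.74 at +3.

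**5. Sensitivity to the assumed baseline.** The gap between the two scorings is (10 − baseline)/38 per death: 4/38 = 0.11 at baseline 6 and 2/38 = 0.05 at baseline 8. For two excess deaths that is 0.11 to 0.21 points, or 7% to 14% of the 1.5-point target.

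**The case against.** **Death is not called missing data.** True: the link is an inference from an unqualified rule and the absence of any rule for death. An analysis plan not shown may supply one. It would, however, have to override a printed sentence rather than fill a gap, so the sentence itself needs correcting.

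**Death is penalised.** A reader might infer that deaths cost an arm nothing. The plan's own figures refute that. Zero change is worse than the result of about 96% of LVRS and 81% of BLVR survivors, and three LVRS deaths at zero would remove 3 × 3.1/38 = 0.24 points of mean benefit. This stands: the fault is too small a penalty.

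**QALYs.** A reader might also infer that patients go on accruing QALYs after death. The documents do not support this. The rule sits with the outcome t-tests, the cost-utility analysis has its own text, and that text does not say how death enters. Whether the rule reaches QALYs is unclear; it plainly covers the EQ-5D-5L change score.

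**Hidden mortality.** The outcome list names no mortality or complication comparison. This article condenses a full protocol that is not shown, so the absence is not an error. The 1-month safety call, the later contacts and the commitment to CONSORT reporting make it unsafe to infer that excess deaths would go unseen.

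**Size.** The numbers of deaths and the baseline are assumed, and the Introduction describes modern surgical mortality as much reduced. This stands: the figures illustrate and do not forecast.

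**Conclusion.** The point holds. The printed rule, followed literally, ranks a death before 12 months above any survivor whose iBODE rises, and does the same on the EQ-5D-5L change score for any survivor who deteriorates. On the planning assumptions this concerns about 4% of LVRS and 19% of BLVR survivors. Death is under-penalised, not unpenalised.

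The bias favours the arm with more deaths, and nothing in the document says which arm that will be. With two excess LVRS deaths at an assumed baseline of 7, the expected difference is 1.34 under the rule and 1.18 with deaths at the worst score, a gap of 0.16 points. The chance of declaring a difference is 88% against 72%. With few or balanced deaths, the expected difference is little affected. Because the rule governs the primary analysis and can be corrected by wording, it should be corrected before the data are analysed by arm.

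**What to change.** 1. State that the zero-change rule does not apply to patients who die.
2. Give a death a value no better than the worst change in any survivor. One way is a worst-rank analysis with death ranked last. Another is to keep the t-test with iBODE 10 at 12 months for deaths, supported by that rank analysis. The support is needed because a score of 10 analysed as change does not guarantee the ordering: a death from baseline 8 is +2, while a survivor who goes from 4 to 7 is +3.
3. Report deaths by arm beside the primary result. Vital status can come from the calls at 1, 6 and 9 months and the visits at 3 and 12 months.
4. In the cost-utility text, state that the zero-change rule does not extend to QALYs and that utility is 0 from the date of death.

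**Cost.** Only analysis wording changes; no new data are needed. The statistical price can be noticeable. Three deaths at +3 in an LVRS arm of 38 give a variance of (35/38) × 3.24 + (35/38)(3/38) × 6.1² = 5.69, so the SD rises from 1.8 to about 2.4. Power also falls: to 72% with two LVRS deaths and none after BLVR, and to 83% with two in each arm. Where deaths are unequal, part of that fall is the intended result of counting them.

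### The arms are compared on change in iBODE by an unadjusted t-test after randomisation stratified by site and iBODE; the test is valid but less precise than a model with baseline iBODE and site.

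*Protocol article*

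**What the plan says.** All references are to the protocol article, under Methods and analysis.

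- Outcomes: "The primary outcome will be the change in iBODE score" at 12 months from baseline, on a scale of 0 to 10.
- Assignment of interventions: 1:1 randomisation in random blocks, and "This will include stratification by site and by iBODE score to ensure matched numbers in both arms with an iBODE score of >7".
- Data collection, management and analysis, on the comparison of arms: "Unpaired t-tests will be used to compare mean response across the two groups: control and intervention". Neither stratification factor is named there, nor is baseline iBODE as a covariate.
- Same section, next sentence: "Mixed linear model procedure will be used to evaluate the effects of predefined covariables on dependent outcome variables". The covariables are not listed, and the sentence does not say that this model supplies the treatment effect.
- Same section, in the cost-effectiveness paragraph: "Multivariate regression analysis will be used to adjust for baseline differences in health status between the trial groups". This is the only place where regression adjustment for baseline is stated.

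**The concern.** Stratified randomisation removes most of the between-arm variation due to the stratification factors. If those factors predict the outcome, an unadjusted t-test still counts their variation in its standard error. The interval is then wider than the design warrants, and the true type I error falls below the nominal 5%.

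The change score raises a separate issue. It does use baseline, but with a slope fixed at 1. When the true slope of 12-month iBODE on baseline is below 1, which regression to the mean on a bounded score makes likely, change remains correlated with baseline. That part of the variance stays in the error term. Chance imbalance in baseline iBODE within a stratum is then over-corrected, and one cut at 7 does not prevent such imbalance.

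At stake is the precision of the primary estimate in a trial of 76 patients.

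**Working it through.** **Inputs from the article (Outcomes).** Difference 1.5 points (3.1 against 1.6), SD of change 1.8, 5% significance, 90% power, 34 per arm, 10% dropout, 76 enrolled. The article does not say whether the test is one- or two-sided; two-sided is assumed.

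**The plan's own figure.**
- Normal approximation: 2 × (1.8 × (1.960 + 1.282) / 1.5)² = 30.3, so 31 per arm.
- Noncentral t: power is 89.8% at 31 and 90.7% at 32, so 32 per arm. The stated 34 is slightly generous and gives 92.3%.
- Dropout: 68 / 0.9 = 75.6, so 76, as stated.

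**Planned analysis at 34 per arm.** Half-width of the 95% interval = t(0.975; 66) × 1.8 × √(2/34) = 1.997 × 1.8 × 0.2425 = 0.872 points.

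**Adjusting for baseline iBODE.** Let r be the correlation of baseline with 12-month iBODE, which the article does not give. Assume equal variances s² at the two times.
- Variance of change: 2s²(1 − r).
- Residual variance after adjustment: s²(1 − r²).
- Ratio: (1 + r)/2. Adjusted SD: 1.8 × √((1 + r)/2).

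With 65 degrees of freedom and 34 per arm:

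| r (assumed) | Variance ratio | Adjusted SD | Half-width | Power for 1.5 points |
|---|---|---|---|---|
| t-test on change | 1 | 1.80 | 0.872 | 92.3% |
| 0.3 | 0.65 | 1.45 | 0.703 | 98.7% |
| 0.5 | 0.75 | 1.56 | 0.755 | 97.4% |
| 0.7 | 0.85 | 1.66 | 0.804 | 95.7% |
| 0.8 | 0.90 | 1.71 | 0.827 | 94.6% |
| 0.9 | 0.95 | 1.75 | 0.850 | 93.5% |

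**Relaxing equal variances.** With k = baseline SD / 12-month SD, the ratio is (1 − r²)/(1 + k² − 2rk).
- r = 0.5: 0.75 at k = 1, 0.89 at k = 0.8, 0.95 at k = 0.7, and 1.00 at k = 0.5.
- r = 0.7: 0.85 at k = 1 and 1.00 at k = 0.7.

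The gain is nil exactly when k = r, because the true slope on baseline, r/k, is then 1.

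**Effect of ignoring the stratification.** Stratified block randomisation was simulated with 68 patients, assuming 5 sites, blocks of 2 and 4, a normally distributed baseline and 4,000 trials per null setting. The Monte Carlo standard error at 5% is √(0.05 × 0.95 / 4000) = 0.34 percentage points.
- Baseline-to-change correlation of size 0.5 (equivalent to r = 0.5 under equal variances): t-test type I error about 4.0%, or 3.5% with a site SD of 0.5 points; coverage 96.0% to 96.5%. The model with baseline and site held about 5% and 95%.
- Correlation of size 0.3: t-test type I error about 4.6%, within simulation error of 5%, or 3.8% with the same site SD.
- No baseline or site effect: the two methods agree, with half-widths of 0.868 (t-test) and 0.876 (model). The difference is the price of the extra terms.

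**The case against.** The strongest reply is that this is a preference for efficiency. The sample size rests on a mean difference and an SD of change, and the t-test examines exactly that quantity, with power above the 90% target. That stands, and it limits the point to a recommended improvement.

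The second reply is that the mixed model may already hold the adjustment, with its predefined covariables listed in a document not shown. The article is silent on whether arm is in that model. But it gives the comparison of groups to the t-test, which is a stated choice of method and not an omitted detail.

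The third reply is that the size of the gain depends on assumptions. That also stands. Entry requires FEV1 below 60% predicted and an MRC score above 3, and these are two of the four iBODE components. Baseline spread may therefore be smaller than follow-up spread, which could reduce the gain. The figures also take 34 complete patients per arm; the effect of the plan's zero-change rule for missing data was not computed.

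A reader might infer more than the article supports:

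- That the result would be biased or the false-positive rate inflated. The test errs on the conservative side.
- That baseline is ignored. The change score subtracts it; only the slope is fixed.
- That a quarter of the patients could be saved. The 0.75 ratio needs both r = 0.5 and equal variances, and the article establishes neither.
- That a term for the iBODE stratum would add further precision. Little is expected once continuous baseline iBODE is in the model.
- That the adjusted economic analysis contradicts the t-test. It serves a different purpose; it shows only that baseline adjustment was considered feasible.

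**Conclusion.** The point holds as one of lost precision. The primary comparison, as written, omits the site and iBODE terms used in randomisation and fixes the baseline slope at 1. Its interval is therefore wider than necessary whenever site predicts change, or baseline does beyond that fixed slope.

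Under equal variances and r from 0.3 to 0.9, the half-width would fall by between 19% (0.872 to 0.703) and about 3% (0.872 to 0.850). If the ratio of baseline to follow-up SD equals r, baseline adjustment gains nothing, and any benefit would come from site, for which the article documents no effect. The direction of the fault is well supported; its size is uncertain. The change is worth making because it costs almost nothing, not because the planned test is invalid.

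**What to change.** State, before the comparison is run, that the primary analysis is a linear model of 12-month iBODE on arm, continuous baseline iBODE and site. Using change as the response gives the same arm effect once baseline is a covariate. Pool small sites or fit site as a random intercept. Report the adjusted difference with its 95% confidence interval.

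Use the same form, each with its own baseline value, for the continuous secondary outcomes: CAT, EQ-5D-5L, residual volume, fat-free mass and physical activity. Keep the unpaired t-test as a supportive analysis, and say what the mixed model is for and which covariables it contains.

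The cost is a change of wording and a few degrees of freedom for site. Baseline iBODE and site are already recorded for stratification, so no new data are needed and the sample size does not change.
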